## Abstract

**Background:**

Sub-optimal parenting is a common risk factor for a wide range of negative health, social and educational outcomes. Most parenting programmes have been developed in the USA in the context of delinquency prevention for targeted or indicated groups and the main theoretical underpinning for these programmes is behaviour management. The Family Links Nurturing Programme (FLNP) focuses on family relationships as well as behaviour management and is offered on a universal basis. As a result it may be better placed to improve health and educational outcomes. Developed in the UK voluntary sector, FLNP is popular with practitioners, has impressed policy makers throughout the UK, has been found to be effective in before/after and qualitative studies, but lacks a randomised controlled trial (RCT) evidence base.

**Methods/Design:**

A multi-centre, investigator blind, randomised controlled trial of the FLNP with a target sample of 288 south Wales families who have a child aged 2-4 yrs living in or near to Flying Start/Sure Start areas. Changes in parenting, parent child relations and parent and child wellbeing are assessed with validated measures immediately and at 6 months post intervention. Economic components include cost consequences and cost utility analyses based on parental ranking of states of quality of life. Attendance and completion rates and fidelity to the FLNP course delivery are assessed. A nested qualitative study will assess reasons for participation and non-participation and the perceived value of the programme to families. By the end of May 2010, 287 families have been recruited into the trial across four areas of south Wales. Recruitment has not met the planned timescales with barriers including professional anxiety about families entering the control arm of the trial, family concern about video and audio recording, programme facilitator concern about the recording of FLNP sessions for fidelity purposes and delays due to the new UK research governance procedures.

**Discussion:**

Whilst there are strong theoretical arguments to support universal provision of parenting programmes, few universal programmes have been subjected to randomised controlled trials. In this paper we describe a RCT protocol with quantitative and qualitative outcome measures and an economic evaluation designed to provide clear evidence with regard to effectiveness and costs. We describe challenges implementing the protocol and how we are addressing these.

**Trial Registration:**

Current Controlled Trials ISRCTN13919732

## Background

Parenting has been shown to play a part in determining future mental health (child and adolescent [1,2] and adult [1,3,4]), health related lifestyles (including healthy eating [5], substance misuse [6] and teenage pregnancy [7]), injury rates [8], aspects of physical health [3,9-12], social competence [13,14] and educational achievement [15,16]. Suboptimal parenting is therefore a risk factor for a wide range of health outcomes and improvements in parenting could contribute to the achievement of a range of current policy goals. Through its impact on educational achievement and social competence, parenting is also a determinant of future employability and thus of social inequalities in future generations. Parenting is by no means the only influence on these outcomes. Both the child's temperament [17] and their genetic makeup play a part together with environmental and social factors. However, there is some evidence to suggest that children with problem temperaments are particularly susceptible to suboptimal parenting [18] and that parenting also interacts with genetic risk [19]. So even in families with the other risk factors, parenting support may be a useful intervention. Parenting is amenable to intervention through group parenting programmes and the evidence base showing that such programmes are cost effective in treating conduct disorder and child behaviour problems is strong [20,21]. There is good evidence that they are also effective in preventing behavioural problems in high-risk groups identified by socio-economic deprivation, ethnic group and experience of life events [22-25]. Most of the evidence base on parenting programmes in the early years relates to two programmes: the Incredible Years (IY) Programme [26,27] developed in the USA and Triple P (TP) [28,29] developed in Australia, both of which are now available in the UK. Both focus on the prevention and treatment of conduct disorder, crime and delinquency [25,29] through a targeted approach.

Parenting interventions can be provided on a universal, targeted or indicated basis. The latter approaches have the strongest evidence base and lowest initial cost [20-25]. However, strong arguments can be advanced to suggest that universal provision increases the likelihood of change in high risk as well as whole population groups [30-32]. Given the range and ubiquity of health and social outcomes on which parent-child relationships have an influence [2,3,5-16], the inefficiency of targeting on the basis of identifiable risk factors [30,31], and the prevalence of sub-optimal parenting [33], universal approaches are appealing. As a result, most current government policies relating to parenting in the UK recognise the need for a universal component [34,35], ranging from provision of information and support to universal access to parenting programmes [36].

Until recently very little rigorous evaluation of effectiveness has been conducted on parenting programmes in the UK, but there has been a significant level of programme development. Several UK developed programmes, including the Family Links Parenting Programme [37] (FLNP), are now widely available. These programmes have much in common with IY and TP but focus more on the quality of the parent-child relationship and the parents' well-being. The FLNP is popular with practitioners who see it as having a distinct contribution to make to promotion of health and well-being. The current evidence base for this programme includes qualitative research showing that parents, recruited through schools, value the programme and perceive it to have an impact on family relationships, children's behaviour and their own mental health [38]; before and after studies in community groups showing impact on self report measures of relationship quality and well-being [39]; and routine evaluation by parents attending programmes showing that the great majority value the programme [40]. None of this evidence allows an estimation to be made of the extent of programme impact relative to changes occurring in a control group or enables economic modelling of the costs and effects necessary to assess the relative value of expenditure on such programmes. Such evidence is essential to inform decision making on the best approach to provision of support for parenting.

Lack of an RCT evidence base makes commissioners reluctant to fund provision of the FLNP and because of concern that the programme might no longer be provided in early years settings in their localities, practitioners and commissioners in four counties in south Wales and the Welsh Assembly Government identified funding to commission an RCT of the programme. As a result of this commissioning process which included national open competition and external, transparent peer review, the trial has been adopted as a Clinical Research Collaboration Cymru (National Institute for Health Research umbrella) portfolio study.

This trial aims

1. To measure the effectiveness of the Family Links Nurturing Programme (FLNP), in securing beneficial impact on parenting and health and social outcomes for young children and their families in the short and medium term.

2. To measure the cost consequences of the FLNP.

3. To investigate the fidelity of programme implementation and delivery by practitioners in the trial sites.

4. To investigate the views of families receiving the FLNP in the trial sites related to perceived value attributed to the programme.

## Methods/Design

The study design is a multi-centre, investigator blind, randomised controlled trial.

### a) Setting

The sample is being recruited from families of children aged 2-4 years in deprived areas of Cardiff, Newport, Torfaen and Caerphilly in south Wales. The sampling approach provides a geographical spread and coverage of different cultural groups and should recruit families representative of the UK population in relatively deprived areas, the group for whom universal programme implementation is most clearly recommended and most likely to prove cost effective.

### b) Sample size calculation

We aimed to recruit 144 families into each of the control and intervention groups (288 in total) This sample size will be sufficient to detect an effect size of 0.4 at 85% power and alpha of 0.05 in the primary outcome measure. An effect size of 0.4 is the level of difference which could be expected on the basis of changes observed on objective measures of parenting in recent UK trials of the IYs programme [25,41], in the majority of trials included in systematic reviews [21,22] and in a before and after study of FLNP [40] using self report measures. The control families are offered FLNP after data collection at six months 'post intervention' is complete.

Since the intervention is offered to groups a cluster design effect is included in the analysis. Such design effects are typically small in parenting programme trials. One recent study of the IYs programme in which both randomisation and intervention were subject to design effects identified intra-class correlations attributable to 'group' effects ranging from 0 to 0.16 [25]. In our study, potential design effects would be attributable to the group-based nature of the intervention only, as randomisation is being undertaken at the level of individual families. If the intra-class correlation in our trial is as high as 0.178, a sample of 288 will be sufficient to detect an effect size of 0.6.

Families who do not attend or dropout will be followed up alongside other families. We anticipate a 20% loss to follow-up at 6 months post-intervention based on the results of other trials [42].

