With five phases we have almost recruited to the sample size estimation of 288, but this has taken a year longer than originally planned. The support of the Trial Steering Committee was important in persuading the County Councils that the research team were doing all that could be done to achieve the necessary level of recruitment and that additional funding was required to extend the recruitment period.

The group based nature of this programme and the fact that programmes can be run only three times a year in term time also presents challenges for recruitment. Unless a parent has been to the first session they cannot join a group, although they can of course drop out. Recruiting too early may mean that families lose interest, by the time the programme starts. This has meant that there are only three windows for recruitment each year. In the first year, one of these windows corresponded to a time in which there was an extremely heavy snow fall and the valleys of South Wales were not easily accessible.

When we designed the trial we assumed that each parenting programme would be filled with trial participants. However because of challenges to recruitment and because groups are not viable with less than six parents many of the 'trial' parenting groups included families who were not part of the trial. We failed to anticipate this and as a result we have had to film and will need to code many more sessions than we originally expected.

A further challenge to studies of interventions which often involve complex changes in behaviour or family relationships is to choose an appropriate outcome measure. Well validated measures are essential for the credibility of the results yet such measures may not capture all possible changes that may occur. For this reason, we have opted to collect multiple outcome measures both self report and objective, but this has increased respondent burden and also researcher time and therefore the cost of the trial. The primary outcome is a composite measure which has worked well in other studies, we have examined the properties of this measure in the baseline data to ensure that it is statistically sound in the current study and presented the findings to the Trial Steering Committee for confirmation of the primary outcome before completion of data collection.

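### The fallback detectable effect of 0.6 at ICC 0.178 fits a design effect on both arms, although the article confines clustering to the intervention arm; on that premise it is about 0.50

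*Protocol article*

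**What the plan says.** Section b) Sample size calculation plans 144 families per arm, 288 in all, described as "sufficient to detect an effect size of 0.4 at 85% power and alpha of 0.05 in the primary outcome measure". It adds: "We anticipate a 20% loss to follow-up at 6 months post-intervention".

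On clustering, it says that "potential design effects would be attributable to the group-based nature of the intervention only", because families are randomised individually. Controls are offered the programme only once the six-month data are in. It cites ICCs of 0 to 0.16 from one earlier trial and then gives the fallback: if the ICC is "as high as 0.178, a sample of 288 will be sufficient to detect an effect size of 0.6". It states no group size, power or formula for this figure.

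Section d) Intervention gives 6 to 10 parents per group. The Discussion says the design assumed groups filled by trial participants, and then reports that "many of the 'trial' parenting groups included families who were not part of the trial".

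**The concern.** If clustering arises only from the delivered groups, a control family belongs to no group at the six-month endpoint, and its design effect is 1. A detectable effect that inflates both arms does not follow from that premise.

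The fallback is the article's only quantified statement of what the trial can detect under clustering. It puts the worst case at 0.6, half as large again as the expected 0.4. A reader weighing a null result would take the trial to be less informative than the stated design makes it.

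**Working it through.** **Inputs from the article:** 144 families per arm; 20% loss, so 144 × 0.8 = 115.2 analysed per arm; effect 0.4, 85% power, alpha 0.05; ICC 0.178; groups of 6 to 10.

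**Assumed:** two-sided test; normal approximation; total SD of 1 in each arm; 85% power carried over to the fallback; m analysed trial families per group. The normal quantiles are 1.960 + 1.036 = 2.996.

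**1. Main figure.** n per arm = 2 × (2.996 / 0.4)² = 112.2, so 113. Allowing for 20% loss, 113 / 0.8 = 141.25, so 142 per arm against 144 planned. This reproduces the plan, with no design effect included.

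**2. Fallback, both arms inflated.** (0.6 / 0.4)² = 2.25. Setting 2.25 = 1 + (m − 1) × ICC gives these ICCs:

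| m | 6 | 7 | 8 | 9 | 10 |
|---|---|---|---|---|---|
| ICC | 0.250 | 0.208 | 0.179 | 0.156 | 0.139 |

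Only m = 8 lands near 0.178. Forwards, the design effect is 1 + 7 × 0.178 = 2.246. The detectable effect is 2.996 × √(2 × 2.246 / 115.2) = 0.592, and power at 0.6 is 86.0%. The printed 0.6 is reproduced.

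**3. Intervention arm only.** The variance of the difference is (DE + 1) / 115.2, where DE = 1 + (m − 1) × 0.178.

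| m | DE | Detectable effect at 85% power | Power at 0.6 | Power at 0.4 |
|---|---|---|---|---|
| 6 | 1.890 | 0.475 | 96.6% | 71.4% |
| 8 | 2.246 | 0.503 | 94.7% | 66.4% |
| 10 | 2.602 | 0.530 | 92.4% | 61.9% |

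For m = 8: 2.996 × √(3.246 / 115.2) = 0.503. A t reference with 40 to 25 degrees of freedom raises this to about 0.515 to 0.523. For comparison, both-arm inflation at m = 8 gives 52.6% power at 0.4.

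**4. What 0.6 would require.** With one-arm clustering, 85% power and the method of step 1, a detectable effect of 0.6 needs about 15.7 trial families per group, above the stated maximum of 10. Conversely, detecting 0.6 at m = 8 needs 81 analysed per arm, or 102 after 20% loss.

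**5. Part-filled groups.** The number of trial families per group is not reported. With an illustrative 4, DE = 1.534, the detectable effect is 0.444 and power at 0.4 is 76.9%.

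**The case against.** The strongest reply is that the sentence is not false. It says that 288 is enough for 0.6, and on the one-arm premise it is more than enough. That stands. A reader might infer from this point that the trial is too small, but the discrepancy is conservative and does not support that.

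The second reply is that the route to 0.6 is inferred. This also stands. Since power is not restated, other combinations come close:

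- Both arms, groups of 10, 80% power: 0.595.
- Both arms, groups of 9, no loss, 90% power: 0.595.
- One arm, 90% power, groups of 9 or 10: 0.559 or 0.573, which round to 0.6.
- One arm, groups of 10, a very conservative t on about 10.5 degrees of freedom: 86.6% power at 0.6.

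Of the variants tried, only groups of 8 in both arms also explain the unusual value 0.178. With the power that the section does state, one-arm clustering does not reach 0.6 for any stated group size under the method that reproduces the main figure.

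Two further inferences are tempting and fail. One is that the Discussion contradicts the calculation. Full groups were the design-time assumption, and the article openly reports that it later failed; that is a disclosed departure. The other is that the multilevel model will wrongly give controls a group variance. Section f) Analysis says nothing of the kind, and section b) places the design effect in the intervention only. Random-effect structure and degrees of freedom are commonly left to an analysis plan.

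Finally, recruitment stood at 287 of 288, so no sample size decision turns on this figure. That limits the consequence to interpretation.

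**Conclusion.** The point holds in a limited form. The fallback of 0.6 at ICC 0.178 does not follow from the article's own statement of where clustering arises. Under that statement the detectable effect at 85% power is about 0.50, with a range of 0.475 to 0.530 for groups of 6 to 10, and slightly higher with a small-sample allowance. The printed figure overstates it by about 0.1 SD (0.6 − 0.503).

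This rests on a two-sided test, 85% power carried over, 20% loss and equal total variance in the two arms. The group size of 8 is an inference. If 8 were the number recruited per group and 20% were lost, 6.4 would be analysed, which stays within the range shown.

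The correction does not rescue the main target in this scenario: power for 0.4 is about 66%, better than the 53% under both-arm inflation but still below 85%. Nothing here shows a faulty analysis model.

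**What to change.** Restate the fallback as a detectable effect of about 0.50 at 85% power for ICC 0.178. Give the assumed group size, the 20% loss and the fact that only the intervention arm is inflated. Add that power for the expected 0.4 in that scenario is about 66%. Because many groups were only partly filled by trial families, recompute both figures with the actual number of trial families per group.

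The cost is a sentence or two and a short recalculation, plus a count of trial families in each group. Recruitment and the planned analysis are unaffected.

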### c) Recruitment

Consecutive parents visiting early years' centres are being approached by practitioners. Those who agree, meet with researchers either in the early years centre or on a home visit to discuss the research and to assess eligibility. A repeat visit is made to those still interested 1-2 weeks later for consent, collection of baseline data and randomisation (via the Warwick Clinical Trials Unit randomisation service) to allocate families to control or intervention groups. In families with more than one parent/parent figure present in the household, both parents are being invited to attend the groups, but data are being collected only from the identified main carer. Families were offered a £20 voucher for each tranche of data. In families with more than one child in the age range, data are being collected for both children. Lack of independence of data from multiple children in one family will be taken into account in the analysis (see below).

### d) Intervention

The FLNP is a ten week programme involving 2 hour sessions each week for groups of 6-10 parents. The programme is structured and aims to provide experiential learning through the use of guided discussion, role play and home work. Parents set targets for themselves each week and report back on progress the following week. The course covers a wide range of behaviours and attitudes which parents may or may not choose to adopt. The ethos of the programme is that to empower parents to bring about changes in family life it is important to invite them to test different approaches and see which they can make work in their families, rather than providing prescriptive instructions.

The four building blocks of the programme are: the development of self-awareness and self-esteem, appropriate expectations, positive discipline, and empathy. The programme is eclectic, drawing on social learning theory and psychotherapeutic insights. It is founded on the belief that empathetic insight into emotional determinants of behaviour is important for both positive relationships and behaviour management. It aims to provide parents with insights into the origins of self-esteem and positive relationships by drawing on their own experiences as children. The programme thus supports parents in improving their own relationships with others as well as with their children. Parents are given a copy of the programme book 'The Parenting Puzzle' [37] and each programme is run by two trained facilitators who receive face to face supervision three times during the course of the programme from an experienced programme facilitator. The capacity to make compassionate relationships with the parents in the groups, to empower and to support them and at the same time provide a tightly run structured group programme is seen as essential to success [26,43].

### e) Outcome measures

Parenting programmes can affect family life and wellbeing in a variety of ways and families may respond differently. No single outcome measure can capture all possible impacts. Our primary outcome measure is a composite index derived from observations made and questions administered during a home visit and recorded according to the HOME inventory [44], and responses to a parent report measure of parent child relations (adapted Mothers' Object Relations Scales (MORS), unpublished data) collected at the same visit. This measure is based on an index developed for the recent 3 year evaluation of Sure Start [45] in the UK which has provided data that are normally distributed and sensitive to change.

To supplement this primary outcome, we have included objective measures of parenting: - a 10 minute video of a mealtime coded according to the Mellow Parenting Scheme [46]. This provides scores on six dimensions of parenting; Anticipation of Child's Needs, Responsiveness, Autonomy, Cooperation, Child Distress and Control/Conflict; and a five minute speech sample capturing the parents' description of their children and their relationship with each child.

We have included a range of validated and well used secondary outcome measures to capture health and wellbeing in parents and children. For child wellbeing we have included PedsQL: parent report [47] and the pre-Parent Account of Child Symptoms (prePACS) [48], a standardised interview covering attentiveness, antisocial behaviour and emotional problems together with mother's rating of the scale of the problem and her capacity to cope. Parental wellbeing is assessed using WEMWBS [49], a 14 item self report measure of positive mental health and wellbeing, Parenting Stress Index [50] and a self report quality of life measure: SF-6D [51]. The PedsQL scale will be used as a parent proxy report of the health related quality of life of their child in order to produce utility estimates for the children in each arm of the study [47].

The objective measures of parenting (the video and speech sample) are collected during a home visit to the families in the two months before the programme starts and again six months post programme. Self-completion questionnaires are collected pre intervention, immediately post intervention, and six months post programme. Videos of parenting and five minute speech samples are coded up by researchers who do not know the families and all data analyses will be carried out blind to group allocation.

Cost consequences are being established using health, social service, educational psychology or criminal justice service contacts for children and parents, and use of voluntary sector services; parental expenditure and time away from work attributable to these events or to involvement in the FLNP. Unit costs will be attached using routine data sources [52]. The cost consequences analysis will provide a clear descriptive summary of the results for each of the outcome measures set against the cost of FLNP.

The views and perceptions of families receiving the programme are being assessed by interviews with 12 parents who decline to take part in the research study to determine possible ways of improving recruitment and 12 intervention group parents representing different cultural and social backgrounds and different experiences (positive and negative) within the group, to gather information on the most and least valued aspects of programme, rating of the facilitators, and ways of improving the programme.

Programme fidelity is being assessed using video recordings of three random sessions in each programme (with parental consent) coded by Family Links staff. In addition both the parent and facilitator evaluation forms for the recorded sessions will be reviewed by Family Links. Uptake rates; attendance rates (number of sessions attended); dropout rates; mother/father ratio of attendees and attendance and dropout by day and time of group are also being measured.

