### f) Analysis

The primary statistical analysis aims to measure effectiveness in a pragmatic real life context; this will be an analysis by allocated treatment (based on all families allocated to the intervention group regardless of whether they attended the programme), using mixed univariate and multivariate analysis of variance, taking into account level of attendance, programme fidelity and differences in the characteristics of the two groups as measured by collection of data from parents at baseline: parental age, marital status, housing tenure, income, ethnicity, parental health (including mental health) and recent stressful life events. As a supplementary analysis the potential of the programme to enable parents to change will be assessed in a regression analysis based on numbers of sessions attended (efficacy analysis).

Secondary analyses will be undertaken of all other outcome measures adopting first an allocated treatment approach using mixed univariate and multivariate methods as above followed by an efficacy analysis.

Intra class correlations will be assessed for all the main outcome measures and multilevel modelling used to take into account any design effects as well as the non independence of data from multiple children in one family.

A cost consequences analysis, which allows an array of outcome measures to be considered alongside the cost of the programme will be undertaken to compare FLNP with no intervention in parents and children from public purse, societal and parents' perspectives. Modelling will examine the sensitivity of the results to a range of assumptions.

Video recordings of sessions will be analysed using an agreed structured coding framework to assess the extent to which facilitators achieved programme fidelity and the skills of the facilitator, with a simple 1-5 fidelity rating applied to each programme.

For the qualitative interviews an iterative thematic analysis will be undertaken using data from all sources independently and results 'triangulated' across these to identify areas of commonality and difference.

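### Analysis cannot be blind to allocation as claimed, because the stated models use attendance and programme fidelity, which have values only in the intervention arm

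*Protocol article*

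**What the plan says.** Section e) Outcome measures of the protocol article first says that videos and speech samples are coded by researchers who do not know the families. It then adds, with no exception, that "all data analyses will be carried out blind to group allocation".

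Section f) Analysis describes the primary analysis as a comparison by allocated treatment, "taking into account level of attendance, programme fidelity and differences in the characteristics of the two groups". A supplementary efficacy analysis regresses outcome on the number of sessions attended. The secondary outcomes are handled "using mixed univariate and multivariate methods as above followed by an efficacy analysis". For clustering, the section plans "multilevel modelling used to take into account any design effects". Fidelity is a rating from 1 to 5 given to each programme delivered.

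Section b) Sample size calculation says that "potential design effects would be attributable to the group-based nature of the intervention only". On timing it says: "The control families are offered FLNP after data collection at six months 'post intervention' is complete".

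**The concern.** A treatment comparison can be run blind if the arms carry neutral labels and nothing else in the file shows which is which. The variables named in f) Analysis appear to break that condition, and they do so in the primary model as well as in the supplementary ones.

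What is at stake is whether a stated safeguard exists. The article presents the trial as investigator blind. It also reports, under the heading on challenges to researchers remaining blind, that some participants disclose their allocation at follow-up visits. The primary composite rests on observations, questions and parent report from a home visit. A reader weighing that weakness may give credit for blind analysis, and should be able to rely on the statement.

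**Working it through.** The article gives no figure on this point to reproduce. The check is whether each variable in the stated analyses exists in both arms.

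**Step 1: the variables side by side**

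| Variable | Where used | Intervention arm | Control arm in the analysed period |
|---|---|---|---|
| Sessions attended | Primary model, efficacy regressions (f) | 0 upwards | Always 0: programme offered only after six-month data (b) |
| Programme fidelity | Primary model (f) | Rating of 1 to 5 per delivered programme | Undefined: no programme delivered |
| Expenditure and time due to programme involvement | Cost analysis (e, f) | May be above zero | None |
| Parenting group | Inferred from multilevel modelling (f) and group-only clustering (b) | Group of allocation | None, but dummy groups could be assigned |

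The first two rows carry the argument. Group membership is not named as a model term and could be masked, so nothing rests on it.

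**Step 2: do masked labels survive?**

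Call the arms A and B. If any family in A has attended a session, A is the intervention arm. The labels stay hidden on attendance only if no intervention family attended at all.

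Inputs: 144 intervention families (b), and q, the probability that an intervention family never attends. The article gives no value for q, so a range is shown. Families are treated as independent.

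P(labels stay hidden) = q^144

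- q = 0.3: 0.3^144 ≈ 5 × 10^-76
- q = 0.5: 0.5^144 ≈ 4 × 10^-44
- q = 0.9: 0.9^144 ≈ 3 × 10^-7

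The result is practically zero at any plausible attendance, so the conclusion does not depend on q.

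**Step 3: which individual families are identified by attendance alone?**

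Without the arm label, only attenders stand out. With equal arms, their expected share of all families is (1 − q)/2:

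- q = 0.3: 0.7/2 = 35%
- q = 0.5: 0.5/2 = 25%
- q = 0.9: 0.1/2 = 5%

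Never-attenders look like controls. Once the arm label is also in the file, as a comparison by allocation requires, Step 2 decodes every family.

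**Step 4: which analyses are affected?**

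- Primary analysis as written: yes, because attendance and fidelity are in it.
- Secondary allocated-treatment analyses: yes, because they repeat the primary methods.
- Efficacy regressions: yes, by construction.
- Cost analysis: yes, through costs due to programme involvement.
- Coding of videos and speech samples: no.
- Work that uses none of these fields, such as deriving the composite index: no.

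**The case against.** The strongest reply is that this is a narrow overstatement. The clause closes a sentence about blind coding, and that coding stands. When the Discussion addresses bias, it relies on outcomes coded blind and on cautious interpretation, not on blind analysts. The composite was checked on baseline data and taken to the Trial Steering Committee for confirmation before data collection ended. An analysis plan that is not shown may fix the models and so limit any harm. All of this is fair, and it bears on how much damage the contradiction does. It does not remove the contradiction: no analysis plan can satisfy both sentences without changing one of them.

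A second reply is that the primary analysis fails only because variables measured after randomisation sit in an allocated-treatment model; take them out and that comparison can be masked. This is correct and is the basis of the fix. It also means that the fix changes the primary model and is more than a rewording.

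A reader might infer three stronger things, none of which the documents support:

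- **That the false-positive rate rises by a calculable amount.** Choosing among models after seeing results is a risk of an open model form. It exists under masked A and B labels too, so it does not measure this defect.
- **That attendance reveals the allocation of nearly every family.** On its own it identifies attenders only, as Step 3 shows.
- **That blinding in the trial is absent altogether.** Blind coding is a separate safeguard and is untouched.

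**Conclusion.** The point holds. The article states a property of all its analyses that its own primary, secondary, efficacy and cost analyses cannot have. For a comparison by arm the loss is effectively complete: masked labels fail with near certainty even if nine in ten intervention families never attend. This assumes that control families have no sessions in the analysed period, as section b) implies, and that attendance or fidelity is in the analyst's file when the models are run. The article describes no step that holds those data back.

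Loss of analyst blinding does not by itself show bias. The consequence is that readers are offered a protection that the stated models rule out, and that could be kept for the main comparisons at little cost.

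**What to change.** 1. In f) Analysis, define the primary and secondary allocated-treatment comparisons with allocation and baseline covariates only, without attendance or fidelity.
2. Run and lock these comparisons under masked arm labels before attendance and fidelity data are linked. Either mask group clustering, for example with dummy groups for control families, or declare that part unblinded.
3. Link attendance and fidelity afterwards, for the supplementary analyses.
4. Restrict the sentence in e) Outcome measures to the coding of recordings and the locked comparisons. State that the efficacy, fidelity and cost analyses are unblinded.

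Writing the analysis script beforehand on a file with permuted allocation, group and attendance fields would be a further precaution, but it is optional.

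The cost is a revised sentence in e), a revised primary model in f) and an order of work for the analyst, with no new data. There are two downsides. The trial can no longer say that every analysis is blind, and attendance and fidelity move from the primary model to supplementary analyses, so the primary model changes. That second change also takes post-randomisation variables out of a comparison meant to count families as allocated, whether or not they attended.
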